### Statistical analysis

#### Primary analysis

The primary analysis will be based on the D1 domain of the MFM in ambulant patients. For both groups A and B, two analysis sets will be built. The full analysis set will include all patients who had at least one follow-up measurement at week 24 or later. The per-protocol set will include all patients from the full analysis set who had the 1-year follow-up visit, and who had a drug compliance of 70–100%. The analysis will be done on the intention-to-treat principle. The measurement at randomization (week 0) will be considered as the baseline and the measurement at week 48 as the primary endpoint. An ANCOVA approach will be used: D1 at 48 weeks will be modeled using a linear regression model including D1 at baseline and treatment groups (verum versus placebo) as predictors in the model. Medication with glucocorticoids will be included as a covariable. Since D1 can be performed only in ambulant patients, this patient group will be used for the primary analysis. The model will be controlled by checking the model assumptions and by inspecting the residuals and leverages.

A following sensitivity analysis will be done to support the main analysis: concomitant use of CYP2D6 inhibitors in the treatment arm as an interaction term, glucocorticoid use in the treatment arm as an interaction term, exclusion of adjustment for glucocorticoid use, exclusion of multiple imputations (the last observation available at least 24 weeks after randomization will be imputed for missing values), inclusion of all measurements at weeks 0, 12, 24, 36, and 48 in a mixed -effects model, and repetition of the analysis on the per-protocol dataset.

For further efficacy analysis, the previously described ANCOVA approach (based on the primary outcome measure) will be performed also for the OLE phase.

#### Secondary analyses

The goal of the secondary analyses is to show superiority of tamoxifen compared to placebo in regard to the secondary objectives. The two patient groups will be analyzed in separate models for all endpoints. The analyses will be performed on the full analysis set and include the following: MFM total score, a subset of D1 domain scores showing a more distinct decrease during disease progression in several datasets, D2 domain, D3 domain, NSAA, TFT, PUL, QMT, qMRI using muscle FF, and PARS-III. The analyses will use the same statistical model as specified for the main analysis; however, in the calculation of the muscle FF, a beta regression model will be performed.

For safety reasons, an interim analysis is planned after the completion of the double-blind phase of the study. The number and type of treatment-emergent as well as treatment-related adverse events will be summarized and compared between treatment groups. A safety analysis will be performed similarly also for the OLE phase.

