### Inclusion criteria

Only male patients with a molecular diagnosis of DMD are included in the study. Ambulant patients in group A must fulfill the following criteria at screening: 6.5 to 12 years of age, weight >20 kg, stable treatment with glucocorticoids >6 months, ability to walk at least 350 m without assistance in 6MWT and a D1 domain of the motor function measure (MFM) >40%. Nonambulant patients in group B must be between 10 and 16 years of age at time of screening, be off glucocorticoids for >6 months, and have no ability to walk more than 10 m. Patients taking ataluren should be under a stable ataluren treatment for at least 3 months or be off ataluren treatment for at least 3 months before screening. For participation in the OLE trial, a preceding completion of the main study is mandatory.

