##### Change in TFT measured by 6MWT, 10MWT and time to rise from the floor under tamoxifen compared to placebo

TFT are useful clinical assessments in ambulant patients since they provide important information about the patient’s endurance. The 6MWT has especially been shown to be a good surrogate marker of disease progression as it independently predicts loss of ambulation [41–44]. A walking distance of <350 m in the 6MWT is considered a strong predictor of clinical decline [41, 42, 45, 46]. TFT of the study will include 6MWT, 10MWT and time to rise from the floor.

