### Sample size estimation

Sample size estimation was performed for the ambulant patients to allow the identification of a significant difference in the D1 domain between the two treatment groups (verum versus placebo). A type I error rate of α = 0.05 was used and the power was set at 1 – β = 0.8. The sample size estimation was based on clinical data from patients in the placebo arm of the Treatment with L-citrulline and metformin in Duchenne muscular dystrophy (DMD02) study [52]. The mean change in D1 domain of these patients was 9.1% during 25 weeks while, previously, an annual D1 decline of 17.2% was reported in ambulant DMD patients [32].

A semiparametric method was performed to account both nonparametrically for the available dataset and parametrically for the treatment shift. Each sample size, *n*i = 1, ..., 50 = 30, ..., 1500, was evaluated by drawing 99 times an individual dataset of size *n*i from the pilot study dataset. Here, *n*i patients were sampled with replacement from a pilot dataset. For each sample, the average disease progression (mean) between baseline and follow-up was estimated. For patients assigned to placebo, the follow-up measurement of the pilot data was used as the expected follow-up measurement. In patients assigned to tamoxifen, the follow-up measurement was recalculated by adding the treatment effect. An analysis of covariance (ANCOVA) model was used to assess whether the D1 domain significantly differed between the two treatment groups after 48 weeks when adjusting for baseline values. Based on the assumption that tamoxifen reduces the mean decrease of D1 by 50% within 1 year, 79 patients should be screened in group A of the study population. A reduction of 50% corresponds to an average loss of 4.5 points in the D1 subscore under verum compared to a loss of 9 points under placebo. Assuming a screening failure rate of 10% and a drop-out rate of 15%, 79 screened patients would result in 71 randomized patients to ensure 60 evaluable patients in total.

Sample size estimation for the nonambulant patient group was based on practical considerations. Group B does not constitute our main study population and is included to obtain some additional safety and efficacy data. Therefore, statistical power calculations were omitted in this population.

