The primary outcome of the study is defined by the MFM, including evaluation of standing and transfer, axial, proximal, and distal motor function. TFT, particularly the 6MWT, are commonly used endpoints in clinical trials; however, most of them can only be performed in ambulant patients and show age dependency due to changes in motor development [41, 42]. According to as yet unpublished data from our group, sample sizes showing a longitudinal treatment response of at least 50% are the lowest if the D1 domain of the MFM or MFM total score is used compared to use of TFT including the 6MWT. MFM is commonly used in the field of neuromuscular disorders and is validated in patients with DMD [21, 22]. MFM is not only a sensitive test with a low inter-rater and intrarater variability, but it also meets a highly important criterion of outcome measures, namely the sensitive prediction of clinical decline and loss of ambulation. Total MFM score of 70% has been described to be predictive for loss of ambulation in 1 year [33]; however, in ambulant patients, the D1 domain seems to be of higher relevance [33, 34]. A D1 domain of 40% or a mean yearly reduction of 17.2% has been described to be predictive for loss of ambulation [33]. Therefore, D1 was chosen to be the primary endpoint for ambulant patients included in the study. In those patients who have already lost ambulation and are therefore not able to perform the test, the assessment of axial and proximal motor function (D2 domain) gives sensitive information about clinical decline [33]. According to this, the D2 domain will be used as the primary endpoint for the nonambulant population of the study. Further clinical outcome measures, including TFT, NSAA and QMT, will be evaluated as secondary endpoints.

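### Time to rise and 10MWT: the stated linear model understates the decline of boys who lose the task; velocity with 0 for inability would keep it in the comparison

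*Protocol article*

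**What the plan says.** Under Secondary analyses, the protocol article lists the timed function tests (TFT) among the endpoints compared on the full analysis set and fixes their model: "The analyses will use the same statistical model as specified for the main analysis; however, in the calculation of the muscle FF, a beta regression". Muscle fat fraction (FF) is the only endpoint taken out of the main model. Primary analysis describes that model: "D1 at 48 weeks will be modeled using a linear regression model including D1 at baseline and treatment groups (verum versus placebo) as predictors", with glucocorticoid medication as a further covariate.

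The TFT outcome section names the components: "TFT of the study will include 6MWT, 10MWT and time to rise from the floor". The 6MWT is a distance. The other two are times.

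On incomplete data, Primary analysis says: "The full analysis set will include all patients who had at least one follow-up measurement at week 24 or later". Multiple imputation appears only in the list of sensitivity analyses, as "exclusion of multiple imputations (the last observation available at least 24 weeks after randomization will be imputed for missing values"), so it is by implication the main approach. The article gives no value for a boy who attends the visit but cannot do the task.

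Group A entry requires "ability to walk at least 350 m without assistance in 6MWT and a D1 domain of the motor function measure (MFM) >40"%. No entry criterion concerns rising from the floor. Secondary analyses also has groups A and B modelled separately for every endpoint, while group B is defined by being unable to walk beyond 10 m.

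**The concern.** A motor score has a floor, so a boy who can do nothing still has a value. A time does not: once he cannot rise, there is no number of seconds. His result is unrecorded because he did badly, so treating it as an ordinary missing value is wrong.

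If tamoxifen slows decline, more placebo than tamoxifen boys will lose the task. Replacing their result with a time typical of boys who can still perform removes part of the very difference the trial is looking for. Seconds cause a second problem: as a boy nears failure his time rises steeply, so a few very slow boys can dominate the residual variance of a linear model.

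At stake is the stated secondary aim of showing superiority on these tests, chiefly on time to rise.

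**Working it through.** **1. The plan's own figures.** 60 / (1 − 0.15) = 70.6, rounded up to 71; 71 / (1 − 0.10) = 78.9, rounded up to 79. The chain of 79 screened, 71 randomised and 60 evaluable reproduces. It concerns D1 only and is not touched by this point. The article gives no figure for any timed test.

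**2. Is loss of function foreseeable?** Entry is at D1 above 40%. The Discussion states: "A D1 domain of 40% or a mean yearly reduction of 17.2% has been described to be predictive for loss of ambulation". Sample size estimation states, the 9 points being the placebo loss: "A reduction of 50% corresponds to an average loss of 4.5 points in the D1 subscore under verum compared to a loss of 9 points". A placebo boy with D1 of 48 at entry who loses the mean 9 points ends at 48 − 9 = 39, below that threshold. So some boys are expected to reach the region of functional loss within 48 weeks. How many lose rising or the 10 m walk is not given.

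**3. What the stated methods do with such a boy.** He still has a D1 score, so he stays in the full analysis set. His week-48 time is absent. Imputation from baseline and treatment uses the relation seen in boys who have a time. Carry-forward uses a time from week 24 or later if he had one, which predates his loss.

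**4. A hand calculation (all inputs assumed).** Let boys who perform average 9 s in both arms and score inability as 30 s. With 10% unable on placebo and 5% on tamoxifen, an analysis of performers omits (0.10 − 0.05) × (30 − 9) = 1.05 s of the difference. With 5% and 2.5% it omits 0.53 s; with 20% and 10%, 2.10 s.

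**5. Simulation (all inputs assumed).** 60 boys, 1:1. Median baseline rise time 6 s (log SD 0.45), unable beyond 30 s, inability permanent. Mean fall in velocity 0.02, 0.04 or 0.06 per second (SD 0.03, 0.04, 0.05), halved by tamoxifen. ANCOVA without the glucocorticoid covariate, two-sided 5% (the article does not state sidedness), 3,000 trials per scenario.

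| | Mild | Middle | Strong |
|---|---|---|---|
| Unable at week 48, placebo / tamoxifen | 3.1% / 0.6% | 8.8% / 1.8% | 16.5% / 4.0% |
| Seconds, boys with a time: difference; power | −0.77 s; 26% | −1.34 s; 39% | −1.68 s; 38% |
| Seconds, multiple imputation | −0.77 s; 26% | −1.34 s; 38% | −1.68 s; 38% |
| Seconds, last value carried forward | −0.94 s; 32% | −1.80 s; 54% | −2.47 s; 64% |
| Velocity, unable = 0: power | 34% | 64% | 78% |
| Worst rank for unable: power | 28% | 56% | 71% |

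Imputation gives the same answer as leaving the boys out. Carry-forward recovers part of the difference, though it still uses times from before the loss.

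**6. Scale or inability?** A second set of assumed scenarios separates the two: baseline velocity 0.20 (SD 0.08) per second; placebo falls of 0.06, 0.08 and 0.05, halved by tamoxifen; SD of change 0.04, 0.05 and 0.035; the same 30 s limit.

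- Seconds in able boys: power 46%, 49%, 44%.
- Velocity in able boys only: 76%, 74%, 73%.
- Velocity with unable = 0: 81%, 83%, 77%.

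The change of scale adds 76 − 46 = 30, 74 − 49 = 25 and 73 − 44 = 29 points. Scoring inability as 0 adds 81 − 76 = 5, 83 − 74 = 9 and 77 − 73 = 4 points. Repeat runs with small coding differences gave 40-47%, 72-76% and 74-83% for the three analyses.

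**The case against.** The strongest reply is that the article fixes a model, not a scale. It does not say that seconds are entered or how inability is coded, and a velocity with 0 would fit the same linear model. Such scoring rules are commonly left to the full protocol, an assessment manual or the SAP, none of which is shown. This stands as a limit: the absence of a rule here does not prove that none exists. What remains is that the article names time to rise as the measure, applies the main model to it and makes an exception only for FF.

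A reader might infer that the worst progressors drop out of all timed tests. The documents do not support that:

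- The 6MWT is a distance and can be 0 m.
- The 350 m entry rule limits loss of the 10 m walk within 48 weeks, so time to rise is the exposed test.
- Imputation is implied, and carry-forward and an all-visit mixed model are listed as sensitivity analyses. The boys are therefore understated rather than lost.
- That some boys lack even a baseline rise time is possible, since rising is not an entry criterion, but nothing in the article shows it.

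A reader might also take the whole power gap as the cost of boys who become unable. Step 6 shows otherwise: most of it there comes from the scale, and those data were generated as normal in velocity, which favours velocity. Log time in able boys alone already gave 64-68%.

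The planned check of residuals and leverages could reveal the very slow boys, but it names no alternative analysis. On group B, the Discussion itself says most timed tests need ambulant patients, and separate models keep group B out of the group A result. The wording on all endpoints is a literal conflict to tidy, not a source of bias.

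**Conclusion.** The point holds for time to rise and, to a lesser extent, for the 10MWT. With the linear model on time and the implied handling of missing values, a boy who loses the task through disease has his decline understated, which biases the comparison toward no effect. Near-failing boys add variance on the seconds scale.

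The size cannot be taken from the documents. Under the assumptions in step 5, the gain from velocity with 0 is small if about 3% of placebo boys lose the task (34.1 − 26.0 = 8 points of power). It is larger at 9% (64.4 − 38.6 = 26 points) and at 17% (78.1 − 38.1 = 40 points), with much of it due to scale.

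The conclusion assumes that no scoring rule for inability exists in the unseen documents. It concerns secondary endpoints only; the primary D1 analysis and the sample size stand. The change is worth making, with medium confidence.

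**What to change.** Under Secondary analyses, or in the SAP before unblinding, state for the timed function tests:

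- Time to rise and 10MWT are analysed as velocity (1/time for rising, metres per second for the walk). A boy unable to do the task because of his disease is scored 0, at baseline as well as at follow-up.
- The 6MWT is scored 0 m in the same case.
- The ANCOVA is unchanged, with the baseline value on the same scale as covariate.
- Imputation is kept for visits not done and for tests not done for reasons other than disease.
- TFT models are fitted in group A only.
- Raw times in seconds, and the number of boys unable per arm and visit, are reported descriptively.

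The cost is a few lines of SAP wording and one code on the case report form that separates inability from a test not done. The downside is an effect expressed in velocity, which clinicians read less readily than seconds; the descriptive table addresses this. If a rule for inability already exists in the full protocol or SAP, it is enough to check it against these points.

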### Quality control and data protection

The clinical study can only begin in a certain country once approval from all required authorities in that particular country has been received. Any additional requirements imposed by the authorities shall be implemented. The safety of the study will be assured by an independent safety monitoring board organized by the CTU of the University Hospital Basel, Switzerland. It will be composed of independent experts to protect the patient’s safety and will also include Duchenne patient organization representatives. An unblinded, independent statistician will be involved. Study monitoring will be performed by the Clinical Research Organization (CRO) multi -service-monitoring ([name]). The monitor will be responsible for controlling the inclusion and exclusion criteria, all patient data, occurrence of serious adverse events, and drug accountability. The CRO SCRATCH Pharmacovigilance GmbH ([name]) will be responsible for serious adverse event processing and keeping the safety database.

Direct access to source documents will be permitted for purposes of monitoring, audits and inspections. The investigators of the study will have access to the protocol and the datasets. The statistician will have access to the statistical code during and after the study. A transfer of data will only take place for study purposes and only in encoded form. For inspection purposes, insight to source data will be permitted to the member of the appropriate authorities and also for members of the local ethics committee. During the study, confidentiality will be guaranteed. The principal investigator will guarantee compliance with national and international data security.

### Storage of biological material and related health data

Biological material and related health data will be stored in an encrypted format for follow-up analyses. Blood samples for biomarker analyses will be stored under standardized conditions at each study center until the last patient visit. Samples will then be sent to the laboratories in Lausanne, Switzerland, to perform the planned, batch-wise analyses.

## Discussion

DMD is a devastating genetic neuromuscular disorder that affects children from their early years of life. Due to their known anti-inflammatory effects, glucocorticoids have been used since the 1980s as a palliative treatment, and their regular intake has been linked to improved muscle strength, muscle function, and even prolonged ambulation [55]. Despite their recognizable advantages in DMD, the extensive side effects of long-term corticosteroid use including weight gain and the high risk for osteoporosis and diabetes mellitus make this therapy option less attractive in patients at a young age. The improved understanding of disease pathophysiological mechanisms led to the initiation of new therapy approaches with the hope of seeing more significant treatment effects combined with better safety. However, most of the novel therapeutic approaches, such as exon skipping therapies or “read through” approaches for mutations, are often applicable to a limited number of patients only because of their mutation-specific functioning.

Tamoxifen, an estrogen receptor modulator used in estrogen receptor-positive breast cancer, is a promising agent and seems to have the potential to reduce disease progression in DMD. Based on encouraging preclinical research data conducted in a mouse model of DMD [21, 22], we aim to test the safety and efficacy of tamoxifen in patients with DMD. Tamoxifen has already been tested in children with brain tumors, pubertal gynecomastia or short height, and showed good safety and tolerability [25–28].

This multicenter, randomized, double-blind and placebo-controlled trial investigates whether tamoxifen can reduce disease progression by at least 50% compared to placebo in 6.5–12-year-old ambulant (group A) DMD patients. The goal of the OLE part is to test if earlier initiation of tamoxifen treatment (patients of the verum arm of the randomized controlled trial phase of this study) can reduce disease progression more efficiently than later treatment onset. Therefore, disease progression during the OLE phase will be compared between both OLE treatment arms. Finally, we also address the question whether tamoxifen can reduce clinical decline in 10–16-year-old nonambulant DMD patients who are not receiving steroids (group B). The inclusion of these patients was highly encouraged by the European Medicines Agency (EMA) in order to obtain more data on safety and efficacy in this patient group, even if statistical significance is not to be expected. The design of this trial, including duration, inclusion and exclusion criteria, efficacy and safety endpoints and statistical analysis regarding sample size and final analysis, have been discussed in detail and agreed with external opinions (Committee for Medicinal Products for Human Use (CHMP) of the EMA, Advisory Committee for Therapeutics (TACT) of Translational Research in Europe for the Assessment and Treatment of Neuromuscular Disease (TREAT-NMD), Sandoz, who are providing the investigational medicinal product, national competent authorities, and responsible ethical committees of the participating countries).

The primary outcome of the study is defined by the MFM, including evaluation of standing and transfer, axial, proximal, and distal motor function. TFT, particularly the 6MWT, are commonly used endpoints in clinical trials; however, most of them can only be performed in ambulant patients and show age dependency due to changes in motor development [41, 42]. According to as yet unpublished data from our group, sample sizes showing a longitudinal treatment response of at least 50% are the lowest if the D1 domain of the MFM or MFM total score is used compared to use of TFT including the 6MWT. MFM is commonly used in the field of neuromuscular disorders and is validated in patients with DMD [21, 22]. MFM is not only a sensitive test with a low inter-rater and intrarater variability, but it also meets a highly important criterion of outcome measures, namely the sensitive prediction of clinical decline and loss of ambulation. Total MFM score of 70% has been described to be predictive for loss of ambulation in 1 year [33]; however, in ambulant patients, the D1 domain seems to be of higher relevance [33, 34]. A D1 domain of 40% or a mean yearly reduction of 17.2% has been described to be predictive for loss of ambulation [33]. Therefore, D1 was chosen to be the primary endpoint for ambulant patients included in the study. In those patients who have already lost ambulation and are therefore not able to perform the test, the assessment of axial and proximal motor function (D2 domain) gives sensitive information about clinical decline [33]. According to this, the D2 domain will be used as the primary endpoint for the nonambulant population of the study. Further clinical outcome measures, including TFT, NSAA and QMT, will be evaluated as secondary endpoints.

Since none of the clinical tests are completely independent of the evaluator’s skills or the patient’s compliance, the analysis of objective surrogate markers is needed. qMRI is a reliable imaging biomarker that can detect even subclinical changes in stable or even improved patients [35, 48, 50, 56]. The muscle FF of the thigh was shown to correlate with disease progression, to predict loss of ambulation and to have strong consistency, especially with the D1 domain of MFM [35, 48, 50, 51, 56]. According to as yet unpublished data from our group, when using the FF of the thigh muscles, a sample size of 6 is sufficient to show disease stabilization due to an active treatment over an observation time of 12 months. In comparison, even the most sensitive D1 domain of MFM requires a sample size of 12, and the total MFM score of 72 to see a treatment effect in 1 year, emphasizing the combination use of both clinical and radiologic outcome measures. Besides efficacy data, regular safety assessments including vital parameters, laboratory values, ophthalmological examination, and evaluation of cognitive function are also included to give useful information about potential risks of the treatment.

Our study not only aims to show safety and efficacy of tamoxifen in children with DMD, but also to gain a better understanding of the mechanism of action of tamoxifen. For this purpose, biomarkers of tamoxifen metabolism and muscle degeneration will be measured throughout the study. The deeper insight into how tamoxifen acts in the muscle might encourage the use of this drug in a broader spectrum of neuromuscular disorders.

